## ANALYTICAL STUDIES

Genomics have emerged as a powerful tool to identify genetic risk factors, both maternal and foetal, of APOs [34-37]. As the association of genetic factors with certain outcomes generally requires a large sample size, the genomics analysis is performed for the full cohort to understand the genetic basis of pregnancy phenotypes and the variation of other omic features. The core steps include the generation of genomic data of maternal and foetal DNA samples using 1 × low-pass whole-genome sequencing, followed by high-quality imputations [38] using large reference panels [39]; conducting genomic analyses of multiple pregnancy phenotypes in mother/infant pairs collected from diverse populations; and integration with other omics measures. Given the close maternal-foetal interaction, pregnancy phenotypes are influenced by both genomes. Therefore, in addition to conventional genomic analysis in mothers and infants separately, the aforementioned genomic analysis will also be conducted in mother/child pairs using a haplotyped-based approach [25], in which a mother-child pair will be treated as the analytical unit with three haplotypes each with distinct maternal or foetal genetic effects. The haplotype-based genomic data analysis will be conducted at three different levels: genome-wide scan for single-variant associations; multi-variant analysis to examine the cumulative effects of multiple variants; and analysis of genome-wide variants to study the genetic architecture (Figure S4 in the **Online Supplementary Document**).

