Epigenomics plays a vital role in understanding how genes interact with environmental factors during pregnancy, significantly influencing maternal and foetal health [40-42]. The MOMI study addresses two key questions in human pregnancy: the association between maternal epigenetic marks and pregnancy outcomes, and foetal epigenetic alterations resulting from suboptimal in utero exposures. The epigenomic analysis will be conducted on a selected subset of approximately 1500 pregnancies, enriched for cases of very PTB, PE, and SB (**Figure 3**). Genome-wide methylation profiling will be performed using the Infinium MethylationEPIC v2.0 BeadChip (Illumina Inc., San Diego, California, USA) on maternal DNA samples extracted from whole blood or buffy coats collected at enrolment, as well as foetal DNA extracted from cord blood or buffy coats (Figure S5 in the **Online Supplementary Document**). Future studies will analyse maternal blood samples collected during follow-up visits to investigate dynamic methylation changes throughout pregnancy. The proposed analytical aims include: testing maternal and foetal DNA methylation associations with pregnancy phenotypes and exposures; developing predictive models for APOs; interrogating methylation associations with maternal exposures, micronutrients, other omics measures; methylation quantitative trait loci (mQTL) analysis and causal inferences by Mendelian randomisation (MR). Although the current epigenomic subset presents power constraints, we will ensure the robustness of our causal inference by restricting analyses to cis-acting mQTLs with high instrumental strength (*e.g.* F-statistics >20) and accounting for ancestry heterogeneity using genetic principal components and stratified sensitivity analyses. With approximately 1500 samples, the study is adequately powered to detect cis-mQTLs explaining approximately 2–5% of methylation variance at stringent genome-wide significance thresholds (α ≈ 5 × 10^−8^). For phenotypic outcomes and MR analyses, this sample size allows for the detection of effects explaining approximately 0.6% of variance at a nominal significance level. To maximise discovery power, we supplement single-site MR with multi-variant approaches, including methylation risk scores and polygenic scores. These analyses are framed as supportive and hypothesis-generating, providing a methodological foundation for future consortium efforts that will expand epigenomic profiling to substantially larger samples.

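### The epigenomic power statement gives direct association and Mendelian randomisation (MR) the same 0.6%-of-variance detectable effect; the figure fits direct association, but MR power for a causal effect of that size depends on instrument strength and is far lower

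*Protocol article*

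**What the plan says.** All of this is in the epigenomics paragraph of the protocol article, section ANALYTICAL STUDIES, unless stated otherwise.

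- The sample: "The epigenomic analysis will be conducted on a selected subset of approximately 1500 pregnancies, enriched for cases of very PTB, PE, and SB".
- The instruments for MR: the plan speaks of "restricting analyses to cis-acting mQTLs with high instrumental strength", with an F statistic above 20 given as an example.
- What can be detected as an instrument: "the study is adequately powered to detect cis-mQTLs explaining approximately 2–5% of methylation variance at stringent genome-wide significance thresholds".
- The next sentence covers phenotypic outcomes together with MR: "MR analyses, this sample size allows for the detection of effects explaining approximately 0.6% of variance at a nominal significance level". It gives no power, and the alpha is described only as "at a nominal significance level".
- The unit of MR analysis: "we supplement single-site MR with multi-variant approaches, including methylation risk scores and polygenic scores".

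The paragraph admits that power is limited in this subset and presents the analyses as exploratory support for later, larger work. In the genomics paragraph of the same section, "the genomics analysis is performed for the full cohort".

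**The concern.** Direct association and MR do not have the same sensitivity at a given sample size. A direct test relates the outcome to measured methylation. MR relates the outcome to the part of methylation that genotype predicts, and the preceding sentence of the article puts the detectable instruments at about 2–5% of methylation variance. Nothing in the paragraph carries that dilution into the MR figure.

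What is at stake is how the MR results are read. A reader told that MR at n of about 1500 detects effects of 0.6% could take a null result as evidence against a causal role. With instruments in the 2–5% range, a null would be expected about nine times in ten even if a causal effect of 0.6% were real.

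**Working it through.** **Inputs.** From the epigenomics paragraph: n = 1500, effect = 0.6% of variance, cis-mQTLs explaining 2–5% of methylation variance, F > 20 as an example threshold. Assumptions: two-sided alpha 0.05 (the article gives no number), a continuous outcome, one instrument, and no path from instrument to outcome except through methylation.

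**Step 1: reproduce the stated figure.** For a direct one-regressor test, NCP = n × R² / (1 − R²) = 1500 × 0.006 / 0.994 = 9.05. Power = Φ(√9.05 − 1.96) = Φ(1.05) = 85.3%; the noncentral F gives 85.2%. The smallest detectable R² is 0.52% at 80% power, 0.60% at 85% and 0.70% at 90%. So 0.6% is the direct-association figure at about 85% power.

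**Step 2: the same effect through an instrument.** If methylation explains R²(causal) of the outcome and the instrument explains R²(inst) of methylation, the instrument explains R²(inst) × R²(causal) of the outcome. Then NCP ≈ n × R²(inst) × R²(causal), and power = Φ(√NCP − 1.96) + Φ(−√NCP − 1.96). The effect detectable with 80% power is (1.960 + 0.842)² / (n × R²(inst)) = 7.849 / (1500 × R²(inst)).

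| Instrument R² | NCP at a 0.6% causal effect | MR power | Causal effect detectable with 80% power | Multiple of 0.6% |
|---|---|---|---|---|
| 2% | 0.18 | 7.1% | 26.2% | 44 |
| 5% | 0.45 | 10.3% | 10.5% | 17 |
| 10% | 0.90 | 15.8% | 5.2% | 8.7 |
| 20% | 1.80 | 26.9% | 2.6% | 4.4 |
| 50% | 4.50 | 56.4% | 1.0% | 1.7 |

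A simulation of 20,000 data sets per setting agrees. The SNP-outcome test rejects in 7.1% (2% instrument) and 10.4% (5% instrument), and the two-stage least-squares Wald test in 5.8% and 10.1%.

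**Step 3: how much the assumptions matter.**
- One-sided alpha of 0.05: power is 11.1% (2% instrument) and 16.5% (5% instrument).
- 80% MR power at 0.6% with n = 1500 needs an instrument R² of 7.849 / (1500 × 0.006) = 87%.
- The example threshold F > 20 admits instruments down to R² = 20 / (20 + 1498) = 1.3%, below the range in the table.

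**Step 4: the other reading.** If 0.6% is the variance explained by the SNP itself, Step 1 applies and power is about 85%. The implied causal effect is 0.006 / 0.02 = 30% of outcome variance for a 2% instrument and 0.006 / 0.05 = 12% for a 5% instrument.

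**Step 5: SNP-outcome associations from the full cohort.** With the 16 221 women of the combined MOMI cohort (Table 2) and a quantitative outcome, the effect detectable with 80% power is 7.849 / (16 221 × 0.02) = 2.4%, or 7.849 / (16 221 × 0.05) = 1.0%. Power at 0.6% is 29% and 60%.

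**The case against.** **The term is undefined rather than wrong.** The sentence speaks of effects explaining a share of variance and does not say a causal methylation effect. Read as the SNP-outcome association, 0.6% is detectable. This stands. A reader might infer that the study lacks the stated MR sensitivity on any reading, and the document does not support that. But the same figure also covers phenotypic outcomes, where 0.6% is naturally the effect itself, and on the SNP-outcome reading the causal effect needed is 12–30% of outcome variance for 2–5% instruments. The article says neither.

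**The 2–5% is a detection range, not a ceiling.** This also stands. A reader might infer that MR power in this study simply is 7–10%. The document does not support that, because stronger cis-mQTLs may exist and the F criterion has no upper limit. The claim has to be conditional on instrument R². Even so, a 50% instrument gives only 56% power at 0.6%.

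**The article already limits its claims.** It concedes limited power, adds multi-variant methods and calls the work exploratory. Nowhere does it say that a null MR result would count against causality. This lowers the weight of the point but leaves the printed number uncorrected, and the multi-variant methods are a supplement to single-site MR.

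**Reach.** A reader might extend the problem to the whole causal programme in DATA ANALYSIS AND DATA INTEGRATION. That is not supported. The causal network search there is a different method, and the MR described there is for molecular traits generally, not only for this methylation subset.

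**Conclusion.** The concern holds in a conditional form. One figure is stated for two analyses and is right for only one of them if it means the effect of methylation on the outcome. At n = 1500, 0.6% fits direct association with 85% power. Single-instrument MR power for a causal effect of that size runs from 7% to 56% as instrument R² goes from 2% to 50%, and is 7–10% only for instruments in the 2–5% range.

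This rests on a two-sided alpha of 0.05, a continuous outcome and one instrument. Correction for multiple testing would lower power further. No figure is given for preeclampsia or other binary outcomes, because the article says only that the subset is enriched for rare cases and does not give their number.

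It is a correction to a stated figure in an exploratory component. It does not invalidate the epigenomic study and need not be ranked among the critical points.

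**What to change.** 1. Limit the 0.6% statement to direct phenotypic association, and give its alpha and power (85% at two-sided 0.05, if that is what was used).
2. State the MR detectable causal effect separately, by instrument R², with alpha and power. At n = 1500, two-sided 0.05 and 80% power this is about 26% of outcome variance at R² 2%, 10.5% at 5%, 5% at 10% and 2.6% at 20%. If the SNP-outcome association was meant, say so and give the causal effect it implies.
3. Add that a null MR result in this subset is uninformative about small effects.
4. Optional: take SNP-methylation associations from the roughly 1500 women and SNP-outcome associations from the full genotyped cohort, allowing for sample overlap. For a quantitative outcome this lowers the detectable effect to about 2.4% (R² 2%) or 1.0% (R² 5%). The gain is smaller for rare outcomes whose cases are already concentrated in the subset.

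Items 1 to 3 cost a few rewritten sentences and a less favourable MR figure. Item 4 needs an added analysis specification but no new samples or assays.

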## DATA ANALYSIS AND DATA INTEGRATION

The analytical objectives of MOMI are to determine the omics signatures of each week of advancing GA (*i.e.* temporal pregnancy progression), the strength of association of each omics or other analytical platform with each APO through machine learning modelling (thereby identifying unique features of each APO phenotype), and how site-specific effects can be used to inform model generalisation. Analysis will proceed systematically from using risk signatures derived from a single platform to signatures identified through integration of multiple omics risk signatures, and from individual cohorts to cross-cohort integration. The integration of phenotypic metadata, including sociodemographics and clinical variables, will further enhance the understanding of biological mechanisms underlying APOs and improve prediction of APOs.

The structural heterogeneity across global cohorts presents a central analytical challenge that will be addressed by explicit methodological safeguards against batch effects, missingness, site heterogeneity, and overfitting. The MOMI analytical framework is built on a mature and extensively validated computational pipeline developed and applied across multiple large, multi-site pregnancy cohorts, including prior MOMI studies [17,19] and in subsequent multi-omic integration and machine-learning frameworks [15,18,20,21]. In these works, we have implemented harmonised preprocessing and quality control, explicit modelling of batch and site effects, and integration strategies that preserve biological signal while mitigating technical variation (*e.g.* empirical Bayes and factor-based normalisation, network-based integration, and multi-view latent variable models). Missing data are handled through a combination of modality-aware imputation and model architectures that accommodate partially observed samples, enabling inclusion of participants with incomplete data without introducing bias.

For non-machine learning association analyses, we will use a prespecified covariate framework grounded in clinical relevance and established epidemiologic confounders, including maternal age, body mass index, parity, GA at sampling, and study site. These variables will be incorporated within mixed-effects or hierarchical regression models to appropriately account for cohort structure and site-level heterogeneity, with model specifications defined *a prior* to avoid data-driven overfitting. To control for false-positive findings across the large number of molecular features tested, we will apply false discovery rate correction within each omics layer and, where appropriate, across integrated analyses.

Although statistical harmonisation approaches such as ComBat are effective at reducing batch effects, they may inadvertently remove meaningful biological or population-level differences between sites. Therefore, our primary framework prioritises external validation across sites as the most conservative test of reproducibility and transportability. Rather than relying solely on post hoc harmonisation, our primary strategy is to evaluate robustness and generalisability directly. Specifically, we will train models on subsets of study sites and validate them on held-out sites. This design allows us to assess real-world performance under true site-level variation, including differences in GA assessment, biospecimen handling, and sociodemographic context. This cross-site training and validation framework ensures that identified signatures are not artifacts of a single cohort, platform, or operational pipeline, but instead reflect patterns that are stable across diverse populations. Only models and associations that replicate across sites will be interpreted as biologically meaningful, providing a principled basis for pooled analyses. As a complementary, secondary analysis, we will apply ComBat-based correction and mixed-effects modelling to quantify and compare the impact of site-level harmonisation. This layered approach allows us to rigorously test whether pooled analyses are justified, distinguish technical from biological sources of heterogeneity, and preserve interpretability, while maintaining statistical rigor across structurally heterogeneous cohorts.

The computational pipeline employs dimensionality reduction and unsupervised clustering for sample classification, followed by statistical modelling to identify signatures associated with adverse outcomes while accounting for confounding factors. Longitudinal analysis characterises trajectories during normal pregnancy progression, providing essential context for understanding pathological changes. In parallel to the statistical approaches, machine learning will be applied to identify signatures with predictive value to enable the development of assays with diagnostic and prognostic value for the identification of APOs. This multi-layered analytical strategy aims to distinguish universal molecular signatures from population-specific variations. Pathway enrichment analysis is an essential step for interpreting the results of predictive models in biological terms, particularly when the aim is to understand the molecular mechanisms of distinct APOs. The different omics platforms will employ distinct pathway analysis tools, such as KEGG Pathway Database, Gene Ontology, STRING, MetaboAnalyst, and others [56-58]. Pathway enrichment will be conducted separately for each site and APO to ensure that the localised biological processes are accurately captured. To predict APOs of interest, machine learning techniques, specifically models based on eXtreme Gradient Boosting [59], a powerful and efficient implementation of gradient boosted decision trees, will be used. For each outcome, a distinct model will be constructed at various pregnancy stages to capture the static risk at that time point. One hundred bootstrap iterations will be performed during which a subset of the patients equal to the size of the full data set will be selected randomly with replacement. This method involves repeated random sampling to split the data into training and validation sets, thus providing a thorough assessment of model performance across various data subsets.

To control for site imbalance in a multi-country cohort, all resampling procedures will be performed using stratified bootstrapping that preserves the joint distribution of site and outcome status. Specifically, bootstrap samples will be drawn within strata defined by study site and outcome (and, where relevant, by case-cohort membership), ensuring that each resample reflects the original cohort’s structural heterogeneity. This approach maintains appropriate representation of under-represented sites and rare outcomes in each iteration, preventing dominance by large sites and reducing bias in variance estimation and model stability assessments. Stratified resampling will be used consistently for uncertainty estimation, feature stability analyses, and performance evaluation, providing a more rigorous assessment of robustness in the presence of site imbalance. The GARBH-INi data will be utilised to validate data generated by the MOMI cohorts and, *vice versa*, GARBH-INi findings may be validated using the MOMI cohort data. The performance of these predictive models will be evaluated using area under the receiver operating characteristic and the area under the precision-recall curve, as well as prevalence of the case. Multi-site analysis is a critical component of model building, ensuring that the predictive models are robust and applicable across different populations and conditions.

A major goal of the MOMI analysis is to move beyond purely associative multi-omics analyses toward mechanistic insight into pathways driving APOs. Thus, we will apply causal inference methods to identify key pathways leading to APOs and inform strategies on their modulation to prevent APOs. Existing causal and footprint-based frameworks (*e.g.* Causal Oriented Search for Multi-Omic Space) were developed primarily in oncology and rely on prior knowledge networks that are sparse for pregnancy biology, omit key pregnancy-specific molecules (*e.g.* pregnancy-specific glycoproteins), and do not natively integrate genomics with multi-omics in this context. We therefore developed Adverse Pregnancy Outcome Learning through a causaL-oriented multi-Omic (APOLLO) search, a pregnancy-aware causal network framework that integrates differential multi-omic signals with curated pregnancy-specific prior knowledge, augmented by data-driven and literature-derived edges. The APOLLO will operate under standard causal inference assumptions (temporal ordering, no unmeasured confounding within modelled graphs, and consistency) and will explicitly encode directionality of regulation. It will be validated by applying it across APOs in the MOMI Consortium and benchmarking its inferred pathways against COSMOS and expert-curated analyses, ensuring that resulting networks are biologically grounded, pregnancy-relevant, and reproducible across sites.

Our planned MR analyses will be guided by a biologically motivated causal framework in which genetic variation precedes molecular variation, which in turn influences pregnancy outcomes. This framework is well supported by prior literature demonstrating causal relationships between genetically regulated trait, such as height, BP, glucose metabolism, lipid levels, and inflammatory processes, and pregnancy outcomes. Where MR is applied, instruments will be selected using established criteria, such as strong association with the exposure (genome-wide significance), independence from confounders, and absence of horizontal pleiotropy (assessed via sensitivity analyses such as MR-Egger and leave-one-out tests). Genetic instruments for molecular traits will be restricted to cis-acting variants where possible to enhance biological interpretability. Together, the MOMI study cohort design and analytical approaches ensure statistical efficiency, cost-effectiveness, and unbiased inference, while enabling robust discovery and validation of molecular signatures across rare and common pregnancy outcomes.

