We hypothesise that the integration of data from multiple omics technologies will provide the means to define biological pathways that are altered in pregnant women with APOs and that, despite some overlap, unique signatures for PTB, PE, stillbirth, and SGA can be deduced to develop novel risk assessment tools and interventions. The inherent heterogeneity across the cohorts in different geographical locations will be counterbalanced by the tightly coordinated study design, data harmonisation, and adjudication of birth outcomes, and the extensively validated computational pipeline developed in prior studies [15-21]. Furthermore, only APO signatures that are reproducible across different cohort sites will be considered biologically and clinically meaningful. This protocol presents the objectives, study design, and analytical approaches of the MOMI Consortium and outlines how integration of multi-omics and metadata will enhance the understanding of pregnancy biology, inform risk prediction models, and contribute to the development of targeted interventions to improve maternal and infant health.

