The probing of longitudinal maternal samples with cord blood and placental tissue at delivery by multiple distinct analytical platforms and the subsequent inter-omics data integration will provide a comprehensive view on normal temporal changes of biological pathways in pregnancies progressing to term and birth of a live infant at appropriate weight *vs.* pregnancies resulting in APOs. While each analytical data set may provide insights into one or more APOs, the power of the study lies in the data integration across multiple platforms that will enable a deeper pathway interrogation and increase confidence into signals associated with APOs. Furthermore, the comparative analysis of data across the various sites will reveal site-specific *vs.* common factors that underlie specific APOs. Site-specific variables, such as genetic background, diet, socio-economic factors, or HIV infection are likely to impact pregnancy outcomes of women in their respective cohorts. Nonetheless, we anticipate identifying signatures common to women with the same APO and specific for that APO. The latter signatures will be most valuable for earlier diagnostics and precision interventions that can improve pregnancy care and outcomes globally. Simultaneously, care can be further improved through additional and complementary site-specific interventions. The data obtained from the placenta analysis are expected to provide novel insights into maternal-foetal interactions and, in combination with the data from the infant follow-up visits, inform about the link between placental function and long-term health risks in offspring. Such knowledge will inform implementation of post-partum interventions to ameliorate long-term health consequences for the infant.

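### Signatures unique to one adverse pregnancy outcome (APO) are inferred from separate per-APO models, and no between-APO contrast is tied to that claim

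*Protocol article*

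**What the plan says.** The introduction's hypothesis is that, "despite some overlap, unique signatures for PTB, PE, stillbirth, and SGA can be deduced". The discussion repeats the expectation: "we anticipate identifying signatures common to women with the same APO and specific for that APO". It ranks these APO-specific signatures as the most valuable for earlier diagnosis and precision intervention.

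The route is given under data analysis and data integration. One objective is the strength of association of each platform "with each APO through machine learning modelling (thereby identifying unique features of each APO phenotype"). Later in that section: "For each outcome, a distinct model will be constructed at various pregnancy stages to capture the static risk at that time point". Pathway analysis follows the same pattern: "Pathway enrichment will be conducted separately for each site and APO".

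The statistical considerations add that the case-cohort design allows comparisons across outcomes through a shared reference sub-cohort. They name no model, test or rule for calling a feature unique. Where the article names a comparator for a specific analysis, it is term birth or normal pregnancy: the nested case-control study, the group II nutrients and the placental studies all compare cases with term births.

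**The concern.** The word *thereby* in the objective is an inference: estimate associations APO by APO, and the unique features follow. They do not. Finding a feature for APO A and not for APO B does not show that its association with A differs from its association with B. The second analysis may simply have had too few cases.

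This study is exposed to that error because its case numbers differ by an order of magnitude, and its own statistical power section says that power depends on the number of outcome events. If specificity is read from separate results, features common to all APOs can be reported as belonging to SGA or PTB. That would be a wrong answer to the stated hypothesis, in the output the discussion values most.

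**Working it through.** **1. Case numbers (Table 2, combined MOMI cohort).** Summing the five sites reproduces the printed totals:
- PTB: 223 + 384 + 366 + 372 + 242 = 1587
- PE: 85 + 35 + 7 + 39 + 124 = 290
- SGA below the 10th percentile: 434 + 936 + 1044 + 683 + 430 = 3527
- Stillbirth: 62 + 25 + 21 + 31 + 29 = 168

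The four sum to 5572, and 5572/16 221 = 34.35%, as printed. SGA has 3527/290 = 12 times the cases of PE and 3527/168 = 21 times those of stillbirth. Because the total is a plain sum, women with two APOs are either counted twice or assigned to one.

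**2. Power for one feature with the same effect on every APO.** The article gives no effect size, reference-group size for this purpose, or false discovery rate level. Assumed here: a standardised shift d, 3000 to 10 000 reference women (the article's random sample is 5000), and two-sided per-feature thresholds of 4.5e-6 (0.05/11 000 metabolomic features), 1e-4 and 5e-4.

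Power = Φ(d/√(1/n_case + 1/n_ref) − z_crit). For d = 0.15, n_ref = 5000 and threshold 1e-4 (z_crit = 3.89):

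| APO | Standard error | d/SE − 3.89 | Power | Range, n_ref 3000-10 000 |
|---|---|---|---|---|
| SGA | 0.0220 | 2.93 | 99.8% | 98-100% |
| PTB | 0.0288 | 1.32 | 91% | 83-95% |
| PE | 0.0604 | −1.41 | 8% | 7-9% |
| Stillbirth | 0.0784 | −1.98 | 2% | 2-3% |

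**3. How often the shared feature looks specific.** Simulating the four estimates with a common reference mean, over all three thresholds and both reference sizes:

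| d (SD) | Found for SGA, not PE |
|---|---|
| 0.15 | 83-98% |
| 0.20 | 55-91% |
| 0.30 | 6-39% |
| 0.40 | 3% or less |

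Stillbirth lags further. At 0.40 SD its power is still 68-95%. SGA detection is then practically certain, so a shared feature is found for SGA but not stillbirth 5-32% of the time.

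**4. Adding a direct contrast.** In SGA minus PE the reference mean cancels, so z = (estimate_SGA − estimate_PE)/√(1/3527 + 1/290), with standard error 0.0611. At threshold 4.5e-6 with 5000 reference women, also requiring this contrast at two-sided 5% cuts the false SGA-not-PE call from 90% to 2.5% at 0.20 SD and from 35% to 2.5% at 0.30 SD. Across the other settings it stays at about 3.5% or less.

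**5. What the contrast can detect.** For a true difference of 0.20 SD between two APOs:

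| Contrast | Power at 5% | Power at 1e-4 |
|---|---|---|
| PE v SGA | 91% | 27% |
| Stillbirth v SGA | 72% | 9% |
| PE v stillbirth | 54% | 3% |

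At 0.05/11 000, PE v SGA has 9% power for 0.20 SD and 63% for 0.30 SD.

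**The case against.** The strongest reply is that a reader may infer more than the article says.

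- **No contrast planned at all.** The text does not support this. The statistical considerations foresee cross-outcome comparisons through the shared sub-cohort, and an article may leave the exact model to an analysis plan. This stands. What remains is that the objective derives uniqueness from the per-APO modelling itself and does not tie the foreseen comparison to it.
- **An explicit present/absent rule.** There is none. The objective speaks of strength of association, which is graded, and the distinct-model sentence concerns prediction. This also stands, but *thereby* still asserts that uniqueness follows, and nothing else in the article says how it would be decided.
- **The figures do not model the planned analysis.** They are univariate tests at assumed thresholds, whereas the predictive models use gradient boosting. They also leave out case-cohort weighting, repeated samples and women with two APOs. They illustrate the mechanism and do not forecast its frequency.
- **The existing safeguards.** False discovery rate control within a layer limits false associations, not false claims of difference. Cross-site replication filters site artefacts, and splitting rare outcomes by site (7 PE cases at one site) makes the imbalance worse.
- **A 5% contrast flatters the remedy.** This is correct. Under multiplicity control the contrast loses much of its power, as step 5 shows.

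**Conclusion.** The point holds in a limited form. Separate per-APO models do not establish uniqueness, and the article states that they yield it. A comparison across APOs is foreseen but not made the basis of the claim.

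The size depends on assumptions: equal effects on all four APOs, 3000 to 10 000 reference women, thresholds of 4.5e-6 to 5e-4, and a univariate test standing in for the real models. On those terms the risk is large for shared effects of about 0.15-0.20 SD and smaller at 0.30 SD. For SGA against PE it is nearly gone at 0.40 SD, while some remains against stillbirth.

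Two stronger readings are not supported. One is that shared features *will* be called unique: that depends on effect size, threshold and a decision rule the article does not state. The other is that uniqueness claims are inflated for every APO. This mechanism runs towards SGA and PTB. With 5000 reference women and a threshold of 1e-4, an equal effect was found for PE but not SGA in under 0.01% of draws (0.15-0.30 SD).

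**What to change.** Replace *thereby* with a rule: a feature or signature is called APO-specific only if a direct between-APO contrast supports it under the plan's false discovery rate control.

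One way is a joint weighted model per feature, with APO indicators against the shared sub-cohort. Women with two APOs would contribute to both indicators. Their handling should be stated in any case, because Table 2 does not show the overlap and the PE criteria include foetal growth restriction and birth weight below the 3rd percentile.

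Where the contrast does not support specificity, report the feature as detected for A, with estimates and intervals for the other APOs. For the machine-learning models, score each APO's model on the other APOs' cases as well as on term controls.

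The cost is wording and some extra analysis of data already collected. Noticeably fewer features will be declared specific, above all for PE and stillbirth, where the contrast has low power at strict thresholds.
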